### Instruments

#### rTMS device

Each stimulation session from the crossover and the longitudinal studies will last 20 min with a frequency of 20 Hz (train duration: 4 s; inter-train interval: 26 s; 3,200 pulses at 120% of the resting motor threshold – RMT, or sham stimulation), adapted from the parameters reported by Legostaeva and colleagues (24) who performed rTMS over the AG in patients with DoC. The RMT (i.e., the minimum stimulus intensity that generated a motor evoked potential response of at least 50 μV at rest for 5 out of 10 trials) will be calculated using single pulses on the corresponding hemisphere of the patient’s dominant hand and reported by a visually detectable twitch in the abductor pollicis brevis muscle. The RMT will be determined at the beginning of each week of treatment with a dedicated round coil, to account for potential changes in the RMT. If a patient presents a high degree of spasticity, or is plegic in the dominant hand, or for any other reason resulting in abnormal corticospinal excitability [which has been described in DoC patients (43)], the other hemisphere will be used for RMT assessment as the RMT calculation is not thought to significantly differ from one hemisphere to the other (44, 45). If the RMT assessment is not conclusive at all, we will rely on RMT data in DoC patients arising from Lapitskaya et al. (43). The associated mean value reported in this article as the mean percentage (%) of maximal stimulator output will be used (i.e., 60%). For the rTMS sessions at both sites, a biphasic stimulator with a capacity up to 100 Hz stimulation will be used (DEYMED diagnostic s.r.o., Hronov, Czech Republic). Stimulations will be delivered through a figure-eight coil with active liquid-cooling (at the Belgian recruiting site) or air-cooling (at the German recruiting sites). Depending on the experimental condition, different coils are used: active stimulation will be delivered via an active rTMS coil, whereas sham stimulation will be delivered via a dedicated sham coil, using the very same parameters. This coil uses a particular shielding mechanism so that no vertical magnetic field is induced. In addition to blocking of magnetic field, the construction of the sham coil makes it suitable for double-blind protocols: since the coil looks the same as the active coil, neither the experimenter nor the patient can see a difference between the coils. The same applies for the acoustic and sensory effect, as there is no difference in the click sound nor in the somatosensory effects. For blinding purposes, a number will be attributed to each coil by the investigator in charge of the randomization. Only the investigator who generated the number assignment will be aware of the allocation and will then disclose the assigned coil number to the investigator in charge of the stimulation the day of the first session.

Structural MRI scans will be used in the crossover RCT to accurately localize the DLPFC and AG (46), using a neuronavigation system that will be connected to the rTMS device (Polaris Vega ST, NDI, Ontario, Canada). In patients without a structural MRI scan, neuronavigation will be performed using a CT scan. In case neuronavigation is not available (e.g., if CT or MRI images could not be obtained), we will target the stimulation area using the 10–20 EEG system electrode positions. The left DLPFC (BA9) can be reached by placing the coil over F3 while the AG has been reported to correspond to BA39, which is under electrode position P3 (47). The cortical structures normally lie within 2 cm of the positions, resulting in 90% accuracy of hotspot detection (48).

Patients are expected to be awake (eyes open) during the rTMS stimulation sessions. If a patient falls asleep, the stimulations will be paused, and the patient will be aroused by auditory or tactile stimulation first. If the patient is still not opening the eyes, the arousal facilitation protocol will be applied according to the CRS-R guidelines (49). The stimulation will resume when the patient opens the eyes again and stimulation time will be adapted accordingly. The patient’s state of arousal will be reported in the Case Report Form for each stimulation session.

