### Population and recruitment

Ninety patients with DoC after severe brain injury will be included in the study. Written informed consent will be obtained from patients’ legal surrogates and the patients themselves if they recover functional communication. The study will be conducted in accordance with the Declaration of Helsinki in its latest form. The study protocol was approved by the University Hospital of Liege Ethics Committee under the reference number 2019/277 (BE021921888) and the Ethics Committee of the Medical Faculty at Ludwig-Maximilians-University Munich under the reference number 20–0873 (Therapiezentrum Burgau and Schön Klinik Bad Aibling-Harthausen) and registered on Clinicaltrials.gov (identifier NCT04401319).

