Eligibility will be derived from medical records and clinical visits. Inclusion criteria will be the following: patients with DoC due to acquired brain injury classified according to international guidelines as UWS/*VS* or MCS with at least two repeated behavioral assessments with the CRS-R within 10 days prior to inclusion; ≥ 18 years old; > 28 days post-injury; and stable vital parameters. As for exclusion criteria, they will be the following: no previous neurological deficits prior to the brain lesions; no pregnancy; no contraindication for TMS (e.g., uncontrolled epilepsy, that is, seizure within 4 weeks prior to enrollment, metallic implant in the skull, pacemaker, craniotomy under the stimulated site, peri-ventricular shunting device, sensitive skin); no sedative drugs or drugs thought to interfere with brain stimulation such as Na or Ca channel blockers (e.g., carbamazepine) or NMDA receptor antagonists (e.g., dextromethorphan); no drugs or substances which have strong potential of seizure induction (imipramine, amitriptyline, doxepine, nortriptyline, maprotiline, chlorpromazine, clozapine, foscarnet, ganciclovir, ritonavir, phencyclidine, ketamine, gamma-hydroxybutyrate, alcohol, and theophylline); and no current enrollment in other therapeutic clinical trial for the whole duration of the treatment protocol and follow-up. Patients will still receive all the standard medical and para-medical care from their facilities such as sensory stimulation or physical therapy. Table 1 summarizes all inclusion and exclusion criteria. In the present study, we will not exclude patients with lesions at the stimulation site (i.e., over the DLPFC or the AG) as it will enable us to document if patients with this structural profile show a lower rate of clinical responders compared to patients with healthy brain tissue at the target location.

**Table 1 tab1:** Study inclusion and exclusion criteria.

Inclusion criteria	Exclusion criteria
Age ≥ 18 years old	Previous neurological deficits prior to the brain lesions
Acquired cerebral damage of known etiology	Pregnancy
Diagnosed in UWS/*VS* or MCS as defined by at least two CRS-R assessments performed during the screening period Time since injury >28 days	Contra-indication for TMS (e.g., uncontrolled epilepsy, that is, seizure within 4 weeks prior to enrollment, metallic implant in the skull, pacemaker, craniotomy under the stimulated site, implanted brain device)

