#### Randomized crossover trial

Within 10 days, all patients will undergo four rTMS sessions that will be administered in a randomized order and separated by a 72 h washout period: (i) one real stimulation over the left DLPFC, (ii) one real stimulation over the left AG, (iii) one sham stimulation over the left DLPFC, and (iv) one sham stimulation over the left AG. In this study, we chose to stimulate the left hemisphere because it tends to be more often targeted in non-invasive brain stimulation trials with DoC patients than the right hemisphere and because it was shown to have more promising results in other top-down electromagnetic-based techniques such as transcranial direct current stimulation (40). Randomization of the sequence of the four stimulation sessions will be stratified for gender, etiology, time post-injury, and diagnosis using computerized random number generator. Standardized behavioral assessments will be performed by experienced clinicians who will be blind to the nature of the sessions. The CRS-R will be performed before and after each stimulation session. Fifteen minutes of resting state high-density EEG will be performed directly before and after the stimulation (i.e., after the behavioral evaluation pre-stimulation and before the behavioral evaluation post-stimulation). Together with the EEG, electrooculogram (EOG) and electrocardiogram (ECG) will be recorded. See Figure 2 for the randomized crossover trial protocol.

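### Both targets are in the left hemisphere, but intensity is set first from the dominant hand's hemisphere, so a left-handed patient measurable on both sides is dosed from the unstimulated side

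*Protocol article*

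**What the plan says.** Under Randomized crossover trial the protocol states "In this study, we chose to stimulate the left hemisphere", and all four sessions, active and sham, are on the left DLPFC or left AG. Personalized parallel trial keeps the same two left-sided targets for the 20-day treatment.

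Under rTMS device, the intensity is 120% of RMT, and the RMT is "calculated using single pulses on the corresponding hemisphere of the patient’s dominant hand". The side changes only for marked spasticity, paralysis of the dominant hand, or another cause of abnormal corticospinal excitability. In those cases "the other hemisphere will be used for RMT assessment as the RMT calculation is not thought to significantly differ from one hemisphere" to the other. If neither side gives a conclusive value, a published mean for DoC patients, 60% of maximal stimulator output, is used. The threshold is renewed weekly: "The RMT will be determined at the beginning of each week of treatment". For the control condition, "sham stimulation will be delivered via a dedicated sham coil, using the very same parameters".

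Handedness is neither an eligibility criterion (Table 1) nor one of the stratification factors of the crossover.

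**The concern.** Thresholding scales the dose to the excitability of the tissue being treated. For a right-handed patient the rule starts on the treated side. For a left-handed patient it starts on the untreated side, and a measurable left threshold does not change that. Nothing in the protocol explains why the untreated side should be preferred when the treated side is available.

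These patients have acquired brain injury, which can be asymmetric, and the protocol itself notes that abnormal corticospinal excitability has been described in them. If the right threshold is higher than the left, the left cortex receives more than the intended 120%. The protocol takes seizure risk seriously: it excludes patients with recent seizures and those on drugs with strong seizure potential. If the right threshold is lower, the patient is under-dosed.

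**Working it through.** **What the plan fixes.** The pulse count reproduces: a 20-minute session has 1,200 s / (4 s + 26 s) = 40 trains, each of 4 s × 20 Hz = 80 pulses, and 40 × 80 = 3,200, as stated. This does not depend on the side of the threshold. Only the intensity does.

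**Which side is used under the current rule, against a left-first rule** (treated side always left):

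| Patient | Current rule | Left-first rule |
|---|---|---|
| Right-handed, left threshold measurable | left | left |
| Right-handed, right hand plegic | right | right |
| Left-handed, both sides measurable | **right** | **left** |
| Left-handed, left hand plegic or spastic | left | left |
| Left-handed, left threshold not measurable | right | right |
| Neither side conclusive | 60% of output | 60% of output |

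Only the third row changes.

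**How many patients.** Sample size from Population and recruitment: "Ninety patients with DoC after severe brain injury will be included in the study". The documents give no share of left-handers, so 5%, 10% and 15% are assumed:

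- 90 × 0.05 = 4.5
- 90 × 0.10 = 9
- 90 × 0.15 = 13.5

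That is about 5 to 14. These figures count all left-handers, so they are an upper bound for the third row.

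**What dose they get.** Dose as a percentage of the left RMT = 120 × (right RMT / left RMT). The ratio is not in the documents; 0.8 to 1.2 is assumed:

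- ratio 0.8: 120 × 0.8 = 96%
- ratio 1.0: 120 × 1.0 = 120%, as intended
- ratio 1.2: 120 × 1.2 = 144%

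The dose falls below the left threshold when the ratio is under 1/1.2 = 0.83.

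**Effect on the randomised comparison.** The hemisphere rule is the same for active and sham, sham is run at identical settings, and in the crossover each patient receives both sites in both active and sham form. The rule therefore does not favour one arm over another.

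**The case against.** The strongest reply is that the protocol has answered the side question: it holds, with citations, that RMT does not differ significantly between hemispheres. If that is true of these patients, the ratio is 1 and nobody's dose changes. Nothing in the documents shows otherwise, so the 96% to 144% range illustrates what could happen and is not an estimate. That stands. But the statement is offered to justify switching when the dominant side fails. It gives no reason to prefer the untreated side when both can be measured. If the sides are equal, measuring the left first costs nothing; if they are not, it corrects the dose.

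A second reply is that RMT is measured with a round coil while treatment uses a figure-eight coil, so even a left threshold would not give an exact 120% at the treatment coil. This also stands. The percentages above are relative to the threshold as the protocol measures it, and the coil difference is the same whichever hemisphere is used.

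A reader might infer that the planned comparison of patients with and without a lesion at the target, meant to "document if patients with this structural profile show a lower rate of clinical responders", or the responder profile, is confounded by dose. The documents do not say which patients will be thresholded on the right or given the 60% value, or whether dose at these levels alters response. Neither the size nor the direction of any such effect can be derived, and how to check for it is ordinarily left to the analysis plan.

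**Conclusion.** The point holds as a minor flaw in the dosing rule. Left-handed patients with measurable thresholds on both sides are dosed from the hemisphere that is not stimulated, and no reason is given for this. The reading of the rule is firm. Its size rests on assumptions: at most about 5 to 14 of 90 patients at 5% to 15% left-handedness, and 96% to 144% of the left threshold for a right-to-left ratio of 0.8 to 1.2.

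It would be wrong to conclude that the active-versus-sham result is biased, or that 5 to 14 is the expected number affected. The first is ruled out by identical settings in both conditions. The second ignores the left-handers who already move to the left, and those whose left side cannot be measured.

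**What to change.** Replace the starting rule with this order, applied at every weekly determination: measure RMT on the left (stimulated) hemisphere in every patient; use the right only if the left is not measurable; use the literature value of 60% of output only if neither is. The same procedure is kept in a different order, so the cost is a short protocol edit and staff instruction. It helps only left-handers with a measurable left threshold. A right-handed patient with a plegic right hand is still dosed from the right hemisphere.

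Optional and secondary: record the source of each patient's threshold (left, right or 60%) at the first measurement, before any stimulation. That is also before the 2:1 randomisation, whereas later weekly values could be affected by treatment. Then check descriptively whether the lesion-at-target and responder-profile comparisons change when all patients not thresholded on the left are left out. Omitting only the 60% patients would miss right-handers thresholded on the right because of left-hemisphere injury. The subset is smaller by an unknown amount, and because an unmeasurable left threshold may itself mark severe injury, the check cannot separate dose from severity.

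### The dose is set as 120% of a resting motor threshold measured with a round coil but is delivered through a figure-eight coil, with no conversion stated, so it is not shown to be 120% of the treating coil's threshold

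*Protocol article*

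**What the plan says.** All of the relevant text is in the protocol article, Instruments, rTMS device.

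- **Dose.** Each 20-minute session at 20 Hz gives "3,200 pulses at 120% of the resting motor threshold", or sham.
- **Threshold.** RMT is defined as the lowest stimulus intensity that meets a motor-response criterion in a hand muscle. On the coil: "The RMT will be determined at the beginning of each week of treatment with a dedicated round coil".
- **Treatment.** "Stimulations will be delivered through a figure-eight coil with active liquid-cooling (at the Belgian recruiting site) or air-cooling (at the German recruiting sites").
- **Sham.** "sham stimulation will be delivered via a dedicated sham coil, using the very same parameters"; the sham coil is shielded.
- **Fallbacks.** If the dominant-hand side cannot be used, the other hemisphere is tested, on the ground that "the RMT calculation is not thought to significantly differ from one hemisphere to the other". If no threshold can be obtained, a published mean of 60% of maximal stimulator output takes its place.

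The article states no conversion, calibration or equivalence between the round coil and the figure-eight coil, in this section or elsewhere.

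**The concern.** RMT is here a machine setting: the protocol defines it as a stimulus intensity and gives its fallback value as a percentage of stimulator output. What a given setting delivers to the cortex depends on the coil. The protocol's own sham method relies on this, since the sham coil runs at the same settings and is built to deliver no effective field. Shielding is an extreme case, but it shows that a setting does not fix the stimulus without the coil. A threshold read on one coil is therefore not automatically the threshold of another.

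Three things depend on the label being true.

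1. **Dose description.** Readers and later trials will take 120% of RMT as the intensity that was tested.
2. **A null result.** If the figure-eight coil has the higher threshold, patients receive less than the label says, and a negative finding could reflect intensity as well as lack of effect.
3. **Safety margin.** If the figure-eight coil has the lower threshold, patients receive more than the label says at 20 Hz. The protocol already treats this population as needing seizure precautions: Population and recruitment requires "no drugs or substances which have strong potential of seizure induction".

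**Working it through.** **Inputs, all from rTMS device:** 20-minute session; 20 Hz; trains of 4 s; intervals of 26 s; 3,200 pulses; intensity 120% of RMT; RMT by round coil; treatment by figure-eight coil; fallback RMT of 60% of maximal output. **Not in the document:** k, the figure-eight threshold divided by the round-coil threshold, both in % output on the same stimulator.

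**Step 1. Reproduce the plan's own figure.** Trains per session = (20 × 60) / (4 + 26) = 40. Pulses per train = 4 × 20 = 80. Total = 40 × 80 = 3,200. This matches exactly, so the pulse count is sound and only the intensity is in question.

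**Step 2. The setting that the text produces.** Setting = 1.2 × RMT(round).

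**Step 3. The same setting on the treating coil's scale.** RMT(figure-eight) = k × RMT(round), so delivered intensity = 1.2 × RMT(round) / [k × RMT(round)] = 120% / k.

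**Step 4. What can be said without knowing k.**

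| Condition | Solve | k |
|---|---|---|
| Label exactly right | 120/k = 120 | 1.00 |
| 10% above nominal (132%) | 120/k = 132 | 0.91 |
| 10% below nominal (108%) | 120/k = 108 | 1.11 |
| Bare threshold (100%) | 120/k = 100 | 1.20 |

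The 10% tolerance is chosen here only to show sensitivity. The table says how close the two thresholds must be for the label to hold. It does not say where k lies.

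**Step 5. The fallback.** If 60% is entered as the RMT, the setting is 1.2 × 60 = 72% of maximal output. The article does not say which coil or stimulator produced the 60%, so its relation to the treating coil's threshold cannot be derived.

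**Step 6. Effect on the comparisons.** In the crossover every patient receives all four conditions in random order. In the parallel trial active versus sham is randomised 2:1. The same intensity rule applies at both sites, and sham uses the same parameters as active. A wrong k changes the active dose in the same way for both targets, so it does not bias either contrast.

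**The case against.** **A journal article condenses the full protocol, and entering a threshold read on one coil for use on another may be an operating detail kept there.** This stands in part: if a validated conversion exists, stating it ends the matter. But the article does more than stay silent. It prescribes the measuring coil and names a different treating coil, so a reader who follows it obtains 1.2 times the round-coil setting. A stated rule that need not deliver the stated dose is more than an omitted detail.

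**No error is demonstrated.** Correct. The two thresholds may coincide. A reader might infer that patients will be under-dosed, or over-dosed, by a known amount; the document supports neither.

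**The paragraph treats RMT as a pragmatic anchor throughout.** Also correct. It carries a hand-muscle threshold to the prefrontal and parietal targets and allows a published mean to replace an individual value. A reader might contrast the referenced between-hemisphere step with the unreferenced between-coil step and see a singular lapse; the text does not bear that out. The coil step differs only in that it can be removed easily.

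**Safety is already covered.** Design plans a new pilot on at least two patients to re-assess tolerability, recent seizure is an exclusion, and all adverse events are graded. These safeguards are real, though a pilot that may be as small as two patients says little about an uncommon event. The safety concern remains conditional on k being below 1.

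**Two further inferences should be resisted.** The different cooling of the Belgian and German coils might suggest a dose difference between countries, but nothing in the document shows that their thresholds differ. And an uncertain dose might suggest biased treatment comparisons, which the crossover, the randomisation and the common intensity rule do not support.

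**Conclusion.** The point holds and should be fixed, with medium confidence. As written, active sessions are set at 120% of the round coil's threshold, which is 120%/k of the treating coil's. The label is exact only at k = 1, and intensity falls to bare threshold at k = 1.20. The document gives no k, so neither the size nor the direction of any error can be stated.

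The conclusion assumes that the round-coil reading is entered without conversion, as the text implies, and that threshold settings can differ between coil types. The validity of the randomised comparisons is not in question. What is at stake is whether the trial can truthfully report its dose, how a null result would be read and, conditionally, the margin at 20 Hz.

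**What to change.** Amend the paragraph so that RMT is determined with an unmasked active figure-eight coil of the same type as the treatment coil at that centre, kept separate from the numbered coded coils. The 120% label is then true by construction. Blinding is preserved: the same open coil is used for every patient whatever the allocation, and no coded coil is used for threshold testing, where a shielded one would be expected to give itself away by producing no response.

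If the full protocol already holds a validated conversion from the round coil, state it and apply it instead. Otherwise, describe sessions dosed from the round coil by % stimulator output and not as 120% of RMT. Do the same for sessions dosed from the 60% fallback, since the coil behind that value is not stated.

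The cost is one additional coil per centre, so three for the centres named under Design, and one amended paragraph. No patients, visits or staff are added, and randomisation is unchanged.
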